## Sample size and statistical analysis

### Sample size

The study was powered for identifying the relationship between plasma sulfate and/or magnesium and the primary outcome, diagnosis of CP (primary aim 1). At the lead study site (MMH), based on audit of data, the CP rate for VP/EP survivors was 7%. The published risk reduction of antenatal MgSO_4_ on CP as per the Cochrane Review of this therapy is 29%.^7^ As such, to determine a clinically significant reduction in the proportion of infants with CP at 2 years CA (7%–5.25%, corresponding to a 30% relative reduction and an OR of 0.74 when sulfate concentration is increased by 1 SD above the mean), and assuming 80% power, a type I error of 0.05 and using plasma sulfate as a continuous predictor, 1324 infants are required. This calculation is based on using logistic regression as the primary analysis technique, and allows for a set of confounders to be included, including plasma magnesium concentration. Allowing for 17% participant loss, including deaths, withdrawals and lost to follow-up, a sample size of 1595 infants will be required.

A sample size calculation for primary aim 2 has not been performed, as the Cochrane Review^7^ was unable to demonstrate a risk reduction effect for intellectual deficits or developmental delay. Cognitive and language delay in VP infants is however much more prevalent than CP, and these outcome measures are continuous variables (standard scores). The sample size calculated for primary aim 1 will therefore be sufficient to detect a clinically significant risk reduction for cognitive/language outcomes if present. Primary aim 3 is predominantly exploratory, and as such a sample size calculation was not undertaken, and p values will not be presented.

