### Statistical methods

#### Primary aims 1 and 2

Descriptive statistics will be used to present the antenatal, intra partum, post partum, neonatal and follow-up characteristics, including plasma sulfate and magnesium concentration, of the cohort. Bivariate relationships will be explored between these characteristics and CP and adverse motor/cognitive/language/behavioural outcomes. Mixed-effects regression models will examine the association between plasma sulfate and magnesium concentrations at 7 days of age with adverse outcomes; site will be included as a random effect, with characteristics known to be associated with the outcome from literature and clinical experience, as well as demonstrating an association in bivariate analyses, included as fixed effects. The number of factors included will be restricted dependent on the prevalence of the outcome. Both unadjusted and adjusted effect estimates will be presented, along with 95% CIs, and p values for the primary model examining CP. An a priori subgroup analysis for <28 weeks versus ≥28 weeks will be undertaken.

#### Primary aim 3

Receiver operator characteristic (ROC) curves will be constructed, using CP/motor delay/cognitive delay/language delay/behavioural difficulties as individual outcomes, and the sulfate concentration as the predictor. The area under the ROC curve (AUROC) will be calculated and presented, along with the 95% CIs. The sulfate concentration that results in the best combination of sensitivity and specificity will be calculated (Youden’s index) for each outcome.

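### The 1324 infants said to allow for confounders are essentially the unadjusted sample size, so the adjusted model has less than the stated 80% power at OR 0.74 unless sulfate is almost unrelated to its covariates

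*Protocol article*

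**What the plan says.** All the inputs are in the Sample size section of the protocol article. From an audit at the lead site, "the CP rate for VP/EP survivors was 7" per cent. The target is given as "7%–5.25%, corresponding to a 30% relative reduction" and as "an OR of 0.74 when sulfate concentration is increased by 1 SD above the mean". The result is stated as "assuming 80% power, a type I error of 0.05 and using plasma sulfate as a continuous predictor, 1324 infants are required". The next sentence names logistic regression as the primary technique and says that the calculation "allows for a set of confounders to be included, including plasma magnesium concentration". A 17% loss then takes 1324 to 1595.

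The section states no R-squared of sulfate on the other covariates and no variance inflation factor. It does not say whether the test is one- or two-sided.

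Under Statistical methods (primary aims 1 and 2) the analysis is a mixed-effects regression: "site will be included as a random effect, with characteristics known to be associated with the outcome from literature and clinical experience". The number of covariates is to be limited by how common the outcome is. On reporting, the plan is: "Both unadjusted and adjusted effect estimates will be presented, along with 95% CIs, and p values for the primary model examining CP".

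**The concern.** In a logistic model, adjusting for covariates that are correlated with the predictor of interest inflates the variance of its coefficient by about 1/(1 − R²). Here R² comes from regressing day 7 sulfate on the other covariates. A sample size that allows for confounders must therefore exceed the single-predictor size by that factor. The stated 1324 looks like the single-predictor size itself.

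The study asks whether sulfate, rather than magnesium, is the protective component. The magnesium-adjusted sulfate coefficient bears most directly on that question, and it is where the variance inflation falls. The Introduction says that antenatal MgSO4 raises neonatal sulfate and largely prevents very low values, so sulfate and magnesium partly share a source. It also describes MgSO4 as standard of care below 30 weeks, which ties exposure to gestation, a likely covariate. If a null adjusted result were read as coming from a test with 80% power at OR 0.74, it would be given too much weight.

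**Working it through.** **Inputs.** From the Sample size section: p = 0.07, OR = 0.74 per SD, power 80%, alpha 0.05, n = 1324. Two-sided testing is an assumption, made because 95% CIs are planned.

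**1. Reproduce 1324 with no covariates.** The Hsieh formula for one standardised continuous predictor is n = (z₁₋α/₂ + z_power)² / [p(1 − p)(ln OR)²].
- (1.960 + 0.842)² = 7.849
- p(1 − p) = 0.07 × 0.93 = 0.0651
- (ln 0.74)² = 0.0907
- n = 7.849 / (0.0651 × 0.0907) = 1330

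The stated 1324 is 0.4% below this. An OR of 0.7395, which rounds to 0.74, gives 1324. The Demidenko (Wald information) method gives 1311 at OR 0.74. The older Hsieh 1989 form gives 1412, which is above 1324.

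**2. Use the stated rates in place of the rounded OR.** The exact odds ratio for 7% to 5.25% is (0.0525/0.9475)/(0.07/0.93) = 0.736. Hsieh then gives 1285 and Demidenko gives 1267.

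**3. Room left for confounders.** Set n₀/(1 − R²) = 1324, so R² = 1 − n₀/1324.

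| Target | Method | n₀ | R² that 1324 allows |
|---|---|---|---|
| OR 0.74 | Hsieh | 1330 | none |
| OR 0.74 | Demidenko | 1311 | 0.01 |
| OR 0.736 | Hsieh | 1285 | 0.03 |
| OR 0.736 | Demidenko | 1267 | 0.04 |

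**4. Consequence at OR 0.74.** Power = Φ(|ln OR| × √[1324(1 − R²) × 0.0651] − 1.96). Required n = 1330/(1 − R²). The detectable OR at 80% power is exp(−2.802/√[1324(1 − R²) × 0.0651]). The R² values are assumptions.

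| R² | Power at 1324 | n for 80% power | Detectable OR at 1324 |
|---|---|---|---|
| 0 | 79.8% | 1330 | 0.740 |
| 0.05 | 77.8% | 1400 | 0.734 |
| 0.1 | 75.6% | 1478 | 0.728 |
| 0.2 | 70.6% | 1662 | 0.714 |
| 0.3 | 64.8% | 1900 | 0.697 |

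Using OR 0.736 in place of 0.74 adds about 1.5 percentage points to each power figure.

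**5. The 30% label.** 7% to 5.25% is 1 − 5.25/7 = 25%, not 30%. A true 30% reduction is 7% to 4.9%, with OR (0.049/0.951)/(0.07/0.93) = 0.685. Hsieh then needs only about 840 infants, and 1 − 840/1324 = 0.37. For that effect 1324 gives 88% power at R² 0.2 and 84% at 0.3.

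**The case against.** **Sidedness is not stated.** A one-sided 0.05 test at OR 0.74 needs about 1048 infants unadjusted, so 1324 would allow R² of about 0.21. This cannot be excluded from the Sample size section alone, but it does not fit the planned 95% CIs, and nothing in the article announces a one-sided test.

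**The sentence may mean model capacity.** The sizing for secondary aim 3 uses ten events per variable, and the number of covariates is to be limited by outcome prevalence. With 1324 × 0.07 = about 93 CP cases, roughly nine parameters could be fitted on that rule. That is true, but it does not hold power at 80% for sulfate, and the sentence describes the power calculation.

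**The size of the loss is not known.** The article gives no day 7 correlation between sulfate and magnesium. At R² 0.05 the loss is about two points, and covariates unrelated to sulfate cost little. This stands, and it is why the result is shown as a range.

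**A small allowance may have been made.** 1285/0.97 = 1325, so an R² near 0.03 fits the figures about as well as none. A reader might infer that nothing at all was added. The documents do not support that. They support only that any allowance was very small.

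**This is a condensed article.** The full protocol could hold an assumed R². That would not change what 1324 can contain given the inputs printed beside it.

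**Conclusion.** The point holds. With the stated inputs and a two-sided 0.05 test, 1324 is essentially the unadjusted single-predictor size, with room for an R² of at most about 0.03 to 0.04. Because sulfate and magnesium share the antenatal infusion as a source, a larger R² is likely, though the article does not quantify it. Adjusted power at OR 0.74 would then be about 76%, 71% or 65% at assumed R² of 0.1, 0.2 or 0.3.

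A reader might go further and infer that the study is underpowered for its headline 30% reduction. The documents do not support that: for a true 30% reduction, 1324 keeps 80% power up to R² of about 0.37. The shortfall applies to the 25% effect that the figures 5.25% and OR 0.74 describe, so how far it matters depends on which of the two conflicting targets is meant.

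**What to change.** 1. State that 1324 gives 80% power for OR 0.74 for the unadjusted association, two-sided if that is what was used.
2. Delete the confounder allowance, or qualify it by giving the assumed R².
3. In the same sentence, resolve the conflict between the 30% reduction and the 5.25% rate with OR 0.74, and carry the result through to the Abstract and the strengths and limitations list, which repeat the 30%.
4. Regress day 7 sulfate on magnesium and the planned covariates in the collected data, without using outcomes. Report the R² and the detectable OR for the adjusted model: about 0.71 at R² 0.2 and 0.70 at 0.3.

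The cost is a few sentences and one regression. The stated power becomes slightly less favourable. No infants are added and the planned analysis does not change.

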### Sample size considerations for secondary aims

#### Secondary aim 1

Using data obtained in a pilot study undertaken at the lead study site (online supplemental file 1), 231 infants exposed to antenatal MgSO_4_ are required to produce a two-sided 95% CI (SD 154, CI width 40). Additionally, 160 infants *not* exposed to antenatal MgSO_4_ are required to produce a two-sided 95% CI (SD 32, width 10).

#### Secondary aim 2

The sample size is based on the combined allelic frequencies of the *SLC13A1* (0.26% p.Arg12Ter and 29.5% p.Asn174Ser) and *SLC13A4* (0.05% p.Ser139Valfs, 0.02% p.Leu72Serfs and 0.05% p.Phe309Cys) gene variants from the NCBI database, and data from a pilot study undertaken at the lead study site showing low neonatal blood sulfate concentrations at 7 days in 10/21 (48%) and at 28 days in 5/15 (33%) of infants whose mothers received MgSO_4_ (online supplemental file 1). Since this aim encompasses two time points, the type I error will be set at 0.025 rather than 0.05 (using Bonferroni’s correction). Additionally, assuming power of 90%, 30% of infants will have a gene variant and in this group 90% will have low sulfate, compared with 30% in the non-variant group, 60 infants and their mothers will need to be included in the study at 7 days of age. At 28 days of age, with the same parameters, however, if fewer infants with a gene variant (80%) have low sulfate and more infants without a gene variant (20%) have low sulfate, 35 infants are required. These infants will be a subset of secondary aim 3.

#### Secondary aim 3

Using data obtained in a pilot study undertaken at the lead study site (online supplemental file 1), 121 infants exposed to antenatal MgSO_4_ are required to develop a multivariate model to assess the relationship between low plasma sulfate concentration with the dose of MgSO_4_ administered, FEI sulfate in the first week after birth, sampling time-point and absence or presence of known loss of function mutations, using the assumption that ten infants with low sulfate are required for potential independent variables.

Blood and urine samples from 300 infants (with or without antenatal MgSO_4_ exposure) taken within 24 hours after delivery, and at 3, 7, 14, 28 days of age will provide sufficient data to create and fit a population pharmacokinetic model for sulfate in the preterm infant using non-linear mixed-effects modelling.^55 56^

#### Secondary aim 4

A sample size calculation for secondary aim 4 has not been performed, as there is no information regarding a relationship between antenatal MgSO_4_ and IVH/ROP/haemangiomas. Results presented will be noted as exploratory.

### Statistical methods

#### Primary aims 1 and 2

Descriptive statistics will be used to present the antenatal, intra partum, post partum, neonatal and follow-up characteristics, including plasma sulfate and magnesium concentration, of the cohort. Bivariate relationships will be explored between these characteristics and CP and adverse motor/cognitive/language/behavioural outcomes. Mixed-effects regression models will examine the association between plasma sulfate and magnesium concentrations at 7 days of age with adverse outcomes; site will be included as a random effect, with characteristics known to be associated with the outcome from literature and clinical experience, as well as demonstrating an association in bivariate analyses, included as fixed effects. The number of factors included will be restricted dependent on the prevalence of the outcome. Both unadjusted and adjusted effect estimates will be presented, along with 95% CIs, and p values for the primary model examining CP. An a priori subgroup analysis for <28 weeks versus ≥28 weeks will be undertaken.

#### Primary aim 3

Receiver operator characteristic (ROC) curves will be constructed, using CP/motor delay/cognitive delay/language delay/behavioural difficulties as individual outcomes, and the sulfate concentration as the predictor. The area under the ROC curve (AUROC) will be calculated and presented, along with the 95% CIs. The sulfate concentration that results in the best combination of sensitivity and specificity will be calculated (Youden’s index) for each outcome.

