## Methods

Prospective observational study at three tertiary NICUs in South-East Queensland, Australia: Mater Mothers’ Hospital (MMH)—lead study site, Royal Brisbane and Women’s Hospital (RBWH) and the Gold Coast University Hospital (GCUH).

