### Recruitment

Women and their partners (‘parents’) are approached before or after delivery to explain the study, and consent is sought within the first few days after delivery.

Recruitment commenced at MMH in July 2015 and at RBWH in August 2015. To accelerate recruitment, the study was expanded to GCUH in June 2019.

Parents of surviving infants recruited into a pilot study of postnatal sulfate concentrations conducted at the lead study site in 2013–2014 (N=52) were contacted for consent to follow-up and inclusion in this study.

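### Site is a random effect with only three levels, so its variance is often estimated at zero and the CP model then carries no site adjustment; fixed site terms avoid this at small cost in the full cohort (minor).

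*Protocol article*

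**What the plan says.** The Methods section of the protocol article describes a "Prospective observational study at three tertiary NICUs in South-East Queensland, Australia" and names all three. Two began recruiting in mid-2015. On the third, the Recruitment section says "To accelerate recruitment, the study was expanded to GCUH in June 2019". The abstract puts the last births in 2020.

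Under Statistical methods, Primary aims 1 and 2, the models are mixed-effects regressions in which "site will be included as a random effect". Characteristics known to matter and associated with the outcome in bivariate analysis enter as fixed effects. Model size is limited: "The number of factors included will be restricted dependent on the prevalence of the outcome". The article gives no fallback for a zero site variance and no analysis with fixed site terms.

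The Sample size section relies on ordinary logistic regression and does not mention site.

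**The concern.** A random intercept for site does three things that fit poorly here. It treats the three units as draws from a wider population, it estimates a variance from three values, and it assumes that the site effects are unrelated to sulfate. In an observational cohort, site is better seen as a possible confounder to be removed.

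The article gives some reason to doubt that site and sulfate are unrelated. Blood is processed and stored at each site before transport to the lead site for assay. The pilot infants of 2013–2014 come only from the lead site. The third site contributes only late births. By the stated timeline its infants reach 2 years corrected age from about August 2021, after the Bayley edition had changed.

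When the site variance is estimated at zero, the likelihood is that of a logistic model without site. A result reported as allowing for site would then not do so. When the variance is positive but small, site differences are shrunk and only partly removed.

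**Working it through.** **Inputs from the Sample size section.** Audit data: "the CP rate for VP/EP survivors was 7" per cent. Target effect: "an OR of 0.74 when sulfate concentration is increased by 1 SD above the mean". Error rates: "assuming 80% power, a type I error of 0.05 and using plasma sulfate as a continuous predictor". Result: "1324 infants are required", or 1595 after 17% loss.

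**The plan's own figure.** For one continuous predictor, n = (z₀.₉₇₅ + z₀.₈₀)² / [p(1−p)(ln OR)²].
- OR 0.74: 7.849 / (0.0651 × 0.0907) ≈ 1330.
- OR implied by 7% and 5.25% (0.736): about 1285.
- Both lie within 3% of 1324, and 1324/0.83 = 1595. The figure is reproduced.
- Approximate standard error of the log OR per SD: 1/√(1324 × 0.0651) = 0.108.

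**How often the site variance is zero.** Datasets of 1324 infants, CP 7% and three sites were simulated (1,200–2,000 per scenario). A random-intercept logistic model (Laplace maximum likelihood) was compared with fixed site indicators. Site shares and between-site SD are assumptions, because the article gives neither.

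| True between-site SD (log-odds) | Zero variance, shares 50/40/10 | Zero variance, shares 34/33/33 |
|---|---|---|
| 0 | 82% | 77% |
| 0.1 | 74% | 69% |
| 0.2 | 58% | 51% |
| 0.3 | 43% | 34% |
| 0.5 | 24% | 17% |

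A separate simulation used adaptive quadrature, shares 45/42/13 and 150–160 datasets per scenario. It gave 30–65% zero estimates, so the result does not depend on the Laplace approximation.

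**Consequence for the sulfate estimate.** Shares were 50/40/10, with site 1 differing from the other two by 0.2–0.4 in log-odds of CP and by 0.3–0.5 SD in mean sulfate, in directions that exaggerate a protective effect.

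| | Random site | Fixed site |
|---|---|---|
| Bias in log OR, all runs | −0.007 to −0.022 | +0.001 to +0.004 |
| Bias in zero-variance runs | −0.013 to −0.049 | not applicable |
| Type I error | 5.4–6.5% | 5.4–5.9% |
| Coverage of the 95% CI | 93.5–94.9% | 94.1–95.8% |

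Across both simulations the random-site estimate lay about 0.01–0.03 beyond the fixed-site one. At most that is 0.03/0.11 ≈ 0.27 standard errors. A true OR of 0.74 would then read as 0.74 × e^(−0.01) = 0.73 to 0.74 × e^(−0.03) = 0.72. When site effects on CP were unrelated to sulfate, bias and coverage were practically the same under both models.

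**Cost of fixed terms, full cohort.**
- Sulfate the same at all sites: standard error 0.1079 → 0.1081, +0.2%.
- Half the infants 0.3 SD higher: between-site variance 0.25 × 0.09 = 0.0225, so √1.0225 = 1.011, about +1%.
- Half the infants 0.5 SD higher: 0.25 × 0.25 = 0.0625, so √1.0625 = 1.031, about +3%. The simulated rise was 2–3%.
- If site explains 2% of sulfate variance, required n is 1330/0.98 = 1357 and power falls from 79.8% to 79.0%. At 5%, n is 1330/0.95 = 1400 and power is 77.8%.
- Events: 1324 × 0.07 ≈ 93, or about 9 parameters at ten events each (an assumed rule). Two site indicators use 2 of them.

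In the confounded scenarios with OR 0.74, the share of significant results was 75–80% with random site and 70–75% with fixed site. Most of that gap reflects the bias away from 1 in the random-site model, not a loss of information.

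**The case against.** A random site effect is a recognised choice, and the article neither contradicts itself nor miscalculates here. The harm needs sites to differ in both mean sulfate and CP risk, and the article reports neither. Zero estimates are most common where true site differences are smallest, so site is retained more often when it matters more. These points stand and keep the matter minor. They do not remove it: in the confounded scenarios 39–71% of datasets still gave a zero variance, and bias was largest in those.

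Three stronger readings are tempting, and the document does not support them.
- A reader might infer that a zero site variance leaves an unadjusted model. It does not, because the other fixed covariates stay. The simulations had no covariates besides sulfate and site. If case mix explains part of the site differences, the residual bias would be smaller than shown.
- A reader might infer that the third site's late start ties site to pandemic-era ascertainment of CP. The link is partial at best. All plasma is assayed at the lead site, and movement videos are scored by blinded assessors from outside the recruiting centres. One CP definition applies, and the disruption is described for the study generally. The 2020 suspension also came before the third site's 2-year visits.
- A reader might infer that fixed terms are nearly free everywhere. That was shown only for the full-cohort CP model. If the third site holds 10–13% of infants (an assumption), it has about 132–172 infants and 9–12 CP cases, split between the <28 and ≥28 week subgroups.

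**Conclusion.** The point holds as a minor one. With three sites, the stated random effect will often be estimated at zero: about 17–58% of datasets at a between-site SD of 0.2–0.5. The primary CP model then carries no site adjustment. The resulting error is about 0.01–0.03 in the sulfate log OR against a standard error of about 0.11, and type I error stayed at or below 6.5% in the scenarios tried. It would not overturn a clear result.

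These sizes rest on assumed site shares, site CP odds and site sulfate means. If mean sulfate does not differ by site, the two models agree. The argument about three levels carries over to the aim 2 models, but no size was computed for them.

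**What to change.** Under Statistical methods, Primary aims 1 and 2, replace the random site term with site as a fixed effect (two indicator terms) in the full-cohort models for both aims. State that these terms are kept whatever the bivariate screening shows.

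For the <28 and ≥28 week CP models, count CP events by site first and state in advance how site is handled if the third site has too few. If the random effect is kept as primary, the least that would help is to report the estimated site variance and a fixed-site sensitivity analysis.

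The cost is one more parameter than the random effect, a standard error about 0.2–3% larger in the full cohort, and 2 of the roughly 9 parameters that about 93 CP events support. Site terms do not remove calendar-period effects within the two sites that have recruited since 2015, so the change should not be presented as an adjustment for period.
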